**Table 3: Time points for data collection**

|  | **Screening** | **Week 0**  **Baseline** | **Week 1-3** | **Week 3** | **Week 6** |
| --- | --- | --- | --- | --- | --- |
| Number of eligible participants | X |  |  |  |  |
| Number of participants sign the consent form | X |  |  |  |  |
| Reason for ineligibility, refusal | X |  |  |  |  |
| DASS-21 |  | X |  | X | X |
| FACT-G |  | X |  | X | X |
| Karnofsky performance status scale | X |  |  |  |  |
| SRF |  |  | X |  |  |
| Process evaluation (interview) |  |  |  | X |  |

[figure not shown]

**Fig. 2. The Consolidated Standards of Reporting Trial (CONSORT) flow diagram (Schulz et al., 2010)**

1. **Intervention fidelity**

Contamination will be minimized by asking the participants not to share the intervention information with other patients. The research assistants will be chosen to participate in the study if they have a bachelor’s degree or a higher qualification, a minimum five-year experience in oncology and have research experience. They will be trained in the data collection process, interview skills to ensure consistency. Only one intervener will deliver MCP training to the patients. The intervener was trained and received music therapy and PMR certificates. To ensure adherence to intervention protocol, the written intervention manual, the checklist will be used. To prevent loss of contact, at least two phone numbers of the patient and the patient's family will be saved.

1. **Data analysis**

Statistical analysis SPSS version 25 will be used, and an intention-to-treat analysis will be used in line with the CONSORT statement. The chi-squared test or Fisher’s exact test, wherever appropriate will be used for categorical data (e.g. family income, cancer stage), while the continuous variables (e.g. age) will use the independent T-test to test the homogeneity at baseline between groups. Categorical variables will be reported as frequencies and percentages and continuous variables will be presented as mean± standard deviation. A two-tailed, two-sample T-test (normally distributed) or Mann–Whitney *U* test (non-normally distributed) will be used to compare the mean difference of DASS-21, FACT-G and subscales score of Intervention Group and Control Group between baseline (T0) and T1, T2, respectively. Cohen’s d will be used to measure the intervention effect size on anxiety and depression, stress, QoL of Intervention Group and Control Group. A generalized estimating equation (GEE) model will be used to compare the difference in each outcome across different time points.

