**Exclusion criteria**

- The patients cannot understand the study procedures
- Have mental health illness, deafness, blindness
- Be participating in other studies related to psychological issues
- Be receiving anxiety or depression treatment.
- Be participating in relaxation therapy such as yoga, meditation, mindfulness, PMR...
- Have a potential treatment (eg. surgery) or personal plans that will prevent them from practising daily during the 6 weeks of the intervention.

1. **Settings**

Participants will be recruited from four public hospitals, Vietnam National Cancer Institute, Hanoi Oncology Hospital in Hanoi, Bach Mai hospital and Nam Dinh general hospital, Vietnam. These hospitals examine and treat patients from the northern and central provinces of Vietnam.

1. **Study sample**

Basing on the study of K. N. Zhou et al. (2015) the effect sizes of anxiety and depression are 1.72 and 0.74, respectively. Thus, the effect size of depression will be used to calculate the sample size. G*power 3.1 software is used with a type 1 error of 5% (α=0.05) and 90% power (β=0.05), two tails, the sample size is 80. The attrition rate in the study of Liao et al. (2018) was 5% after 8 weeks self-practising MCP at home daily. Thus, the final sample size is 84 and each group is 42. The sample size may be adjusted based on the results of the pilot study.

1. **Randomization and allocation concealment**

Blocked randomisation procedures with a 1:1 allocation will be performed by an independent researcher who will not involve any steps of the study. A randomization list will be computer-generated by using the website at https://www.sealedenvelope.com/simple-randomiser/v1/lists. To prevent the investigator from predicting the treatment sequence, a mix of blocks of sizes 4, 6, 8 at random (Efird, 2011) will be used. Besides, blinding both the sequence of blocks and their block size will be applied to be a more effective protection preventing selection bias (Efird, 2011).

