Sequentially numbered, opaque, sealed envelopes will be prepared. To avoid tampering the creator of the envelope will sign on the back of the envelope (Clark et al., 2020). In addition, security measures will include inserting carbon paper into the envelopes to prevent trans-illumination (Clark et al., 2020). The person who creates and keeps the envelopes will be blinded and not be involved in recruiting participants to prevent the ordering of participants into groups (Efird, 2011). The envelopes that contain the names of the assigned group will be given to each patient after they sign the consent form. The envelopes will be opened only after the envelope has been irreversibly assigned to the participants (Doig & Simpson, 2005).

1. **Blinding**

It is impossible to blind participants or interveners because of the nature of the study (Huang et al., 2010). However, research assistants who assess outcome data, data entry and

analysis will be blinded to avoid the risk of assessor bias. The assistants will not participate in any other stage of implementing the program. The participants will be asked not to share their treatment allocation with the research assistants.

1. **Outcome measures and instruments**

Primary outcomes will include anxiety and depression, stress while the secondary outcome will encompass QoL.

Participants’ characteristic data will be collected via a self-designed demographic sheet which will include age, marital status, education level, employment, family income, stage of cancer, frequency of chemotherapy, treatment regimen.

Anxiety, depression and stress will be measured using the short form of the Depression Anxiety Stress Scale (DASS-21) (Lovibond & Lovibond, 1995). The instrument was translated and used in the Vietnamese population with good internal consistency (Cronbach’s alpha of depression subscale 0.72; Anxiety subscale 0.77; and Stress subscale 0.70, overall 0.88) (Tran et al., 2013). It includes 21 items rating scale, 7 items for anxiety (DASS21-A), 7 items for depression (DASS21-D) and 7 items for stress (DASS21-S). A 4-point Likert-type scale ranging from 0 to 3 was designed on each item, thus each subscale had a score from 0 to 21. The higher the score is the more severe is the anxiety, depression and stress.

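### Significance tests of baseline homogeneity are uninformative after concealed randomisation: at 42 per arm an observed imbalance of up to about 0.43 SD is non-significant (minor)

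*Protocol*

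**What the plan says.** In the protocol's Data analysis section for the full-scale study, baseline comparability is to be tested. For categorical variables, "The chi-squared test or Fisher’s exact test, wherever appropriate will be used for categorical data (e.g. family income, cancer stage"); for continuous ones, "the continuous variables (e.g. age) will use the independent T-test to test the homogeneity at baseline between groups". The section also promises frequencies and percentages, and means with standard deviations.

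The characteristics collected, under Outcome measures and instruments, are "age, marital status, education level, employment, family income, stage of cancer, frequency of chemotherapy, treatment regimen", eight in all. The Study sample section fixes the size: "Thus, the final sample size is 84 and each group is 42". Under Randomization and allocation concealment, "Blocked randomisation procedures with a 1:1 allocation will be performed by an independent researcher", with randomly mixed block sizes and sealed opaque envelopes.

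Outcomes are then compared between arms by a two-sample t-test or Mann-Whitney test on the difference between T0 and T1 or T2. A GEE model across time points is also planned. No covariate is named for either. The protocol does not say what follows from a significant or a non-significant baseline test.

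**The concern.** The test asks whether the arms come from the same population. Concealed 1:1 randomisation has already answered that for age, stage, regimen and the other characteristics fixed before allocation, so each rejection is a chance finding.

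Homogeneity, moreover, is a claim of similarity, and a difference test with no margin cannot establish it. A non-significant result at this sample size is compatible with a sizeable observed imbalance.

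Two things are at stake. A baseline table with no small p-values could be taken as showing that the arms are comparable when a prognostic factor is visibly unbalanced. A table with one small p-value could prompt unfounded doubt about the randomisation, or adjustment chosen after seeing the data. What matters for the estimate is the size of the observed imbalance and how strongly the factor predicts the outcome analysed. A p-value measures neither.

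**Working it through.** **Inputs.** n = 42 per arm and 1:1 allocation (Study sample; Randomization and allocation concealment). Eight characteristics (Outcome measures and instruments). The protocol gives no significance level for the baseline tests, so two-sided 5%, as in the sample size, is assumed.

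**The plan's own figure.** The Study sample section takes a depression effect size of 0.74 from "the effect sizes of anxiety and depression are 1.72 and 0.74, respectively" and states "type 1 error of 5% (α=0.05) and 90% power (β=0.05), two tails, the sample size is 80". A two-sample t-test with d = 0.74, two-sided 0.05 and 90% power needs 39.4, so 40 per arm, or 80. Adding 5% for attrition gives 80 × 1.05 = 84, or 42 per arm. The stated size reproduces at 90% power, that is β = 0.10 and not the printed 0.05. The protocol gives no figure for the baseline tests.

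**1. What passes the t-test.** The standard error of a standardised difference is √(2/42) = 0.218, and t(0.975, 82 df) = 1.989. The boundary is 1.989 × 0.218 = 0.434 SD.
- Observed 0.40 SD: t = 0.40/0.218 = 1.83, p = 0.070, not flagged.
- Observed 0.50 SD: t = 0.50/0.218 = 2.29, p = 0.025, flagged.

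**2. False alarms.** With eight independent tests and correct randomisation, 1 − 0.95⁸ = 1 − 0.663 = 0.337, about 34%. Correlated characteristics would change this figure.

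**3. How often a large imbalance arises.** Under correct randomisation an observed difference of at least 0.40 SD has probability 7.0%. The part that still passes the test (0.40 to 0.434 SD) has probability 7.0% − 5.0% = 2.0%.

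**4. What a passing imbalance does to the planned comparison.** The correlations here are assumptions; the protocol gives none. Let the covariate correlate r_B with the baseline score and r_F with the follow-up score, and let those scores have equal variance and correlate 0.6. The covariate's correlation with change is then

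r = (r_F − r_B) / √(2(1 − 0.6)) = (r_F − r_B) / 0.894.

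With no treatment effect and an observed imbalance of 0.4 SD, the difference in mean change (in SDs of change) is centred at 0.4r with standard deviation 0.218√(1 − r²). It is declared significant beyond about ±0.434.

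| Assumption | r with change | Centre | SD | Rejection rate |
|---|---|---|---|---|
| r_B = r_F | 0 | 0 | 0.218 | 5% |
| r_B = 0, r_F = 0.3 | 0.335 | 0.134 | 0.206 | 7.5% |
| r_B = 0, r_F = 0.4 | 0.447 | 0.179 | 0.195 | 9.6% |
| r_B = 0, r_F = 0.5 | 0.559 | 0.224 | 0.181 | 12.2% |

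A simulation of 40,000 trials per row gave 4.9 to 5.0% for the first row (over r_F = 0.3 to 0.5) and 8.0%, 10.2% and 12.7% for the others. With the covariate in the model, rejection was 4.9 to 5.1% in those last three rows.

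**The case against.** The strongest reply is that this changes no treatment estimate. The tests gate nothing in the protocol, the descriptive statistics are already planned, and an unadjusted analysis of a randomised trial holds its 5% level on average over randomisation. The change from T0 also removes whatever part of a covariate's influence is already in the baseline score. Any covariates for the GEE may be in a statistical analysis plan that is not shown. All of this stands, and it is why the point is minor. The defect is the stated tests, not silence about covariates.

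It may also be said that the tests check the integrity of the randomisation. As such a check they are weak, with roughly a one-in-three false alarm across eight variables and no stated response to one. One qualification belongs here: the Procedure section places the T0 questionnaires after randomisation, so the argument that differences are pure chance applies to the demographic and clinical characteristics and less securely to self-reported scores.

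Three stronger readings are tempting and are not supported:
- **That the tests miss a 0.5-SD imbalance 38% of the time.** That is the type II error for a true population shift of 0.5 SD (power 0.620 at 42 per arm), which sound randomisation excludes. An observed 0.5 SD gives p = 0.025 and is always flagged.
- **That p>0.05 will be used to declare the arms comparable or to decide on adjustment.** The protocol writes no such rule; its wording only invites that reading.
- **That the trial's false-positive rate is inflated.** The 8 to 12% is conditional on one particular imbalance and on a factor that predicts change. The documents do not show that any listed factor does.

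**Conclusion.** The point holds as a minor one. The protocol commits to baseline significance tests that cannot inform a concealed 1:1 randomised trial. At 42 per arm they leave any observed imbalance up to 0.434 SD non-significant, and they would produce at least one p<0.05 in about 34% of sound trials if the eight characteristics were independent.

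The effect on the outcome comparison is conditional. It ranges from none (about 5%) when a factor relates equally to baseline and follow-up scores, to about 8 to 12% when a factor that predicts change is unbalanced by 0.4 SD. These rates rest on the assumed correlations and a two-sided 5% level. Unconditionally, the planned comparison is valid.

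**What to change.** In the Data analysis section:
- Delete the chi-squared, Fisher's exact and t-tests of baseline homogeneity.
- Keep the n (%) and mean and SD by arm, and add standardised differences.
- State that no conclusion about comparability will be drawn from p-values.
- Pre-specify, before outcome data are seen, a short list of covariates already collected: the baseline score of the outcome plus, for example, age and cancer stage. Include them in the model for each outcome whatever the observed imbalance. This fits the protocol's Theoretical framework, which holds that demographic and clinical factors affect the response to stress.

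Adjusting for a T0 score taken after randomisation assumes that knowledge of allocation did not alter it; the planned change score makes the same assumption.

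The cost is a few sentences, a few degrees of freedom and the loss of the p-value column in the baseline table. No new data are needed.

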Three studies (Arakawa, 1997; Song et al., 2013; Yilmaz & Arslan, 2015) showed a significant effect on anxiety. A pool effect size of those studies illustrated a large effect on anxiety (SMD: -1.05, 95% CI −1.33 to −0.76, I^2^= 29%). Arakawa (1997) recruited 60 cancer patients undergoing chemotherapy. A nurse-led PMR with deep breath was given to the patients within 72 hours of hospitalization. The dose was 25 minutes/session and twice/ day. Yilmaz and Arslan (2015) revealed a significant effect of PMR on breast cancer after 3 weeks of practising with 3 times/ weeks. However, Lerman et al. (1990) that delivered 30 minutes of PMR, once/day through three chemotherapy treatments indicated that there was no benefit of PMR on anxiety and depression. Herizchi et al. (2012) showed that although practising PMR two to three times a day could not reduce anxiety, depression and improve QoL after 1 month, it gave opposite results after three months. PMR had no significant effect on QoL on gynaecological cancers and breast cancer patients undergoing chemotherapy (Dikmen & Terzioglu, 2019; Gok Metin et al., 2019).

1. **Effect of MI combined with PMR on anxiety, depression and QoL in cancer patients**

Nurse-led MI combined with PMR (MCP) had a significant effect on anxiety and depression on cancer patients. Study of K. Zhou et al. (2015) which deliver muscle relaxation and music listening simultaneously for 30 minutes twice a day, once in the early morning (6 a.m-8 a.m.) and once in the evening (9 p.m -11 p.m), after radical mastectomy until discharged from the hospital. The results showed that MCP had a large effect size on anxiety (Cohen’s d= 1.74) and medium effect size on depression (Cohen’s d= 0.72).

Moreover, MCP had a strong effect size on depression in comparison to PMR alone (Liao et al., 2018b). A study by Liao et al. (2018b) illustrated that cancer patients do 20-min PMRT followed by 20-min Chinese medicine five-element music at 10 a.m. or 3 p.m, for 8 weeks could reduce depression level rather than PMR alone ( Cohen’s d= 0.9). Thus, the combination of MI and PMR may boost the effectiveness of single interventions (Liao et al., 2018a)

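### The two-arm comparison is an unadjusted change-score test with a normality switch, beside a GEE with no stated baseline adjustment, and the protocol does not say which analysis decides

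*Protocol*

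**What the plan says.** The Data analysis section of the protocol names two kinds of between-arm analysis for DASS-21, FACT-G and their subscales.

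- A two-sided two-sample t-test where data are normal, or a Mann-Whitney U test where they are not, "will be used to compare the mean difference of DASS-21, FACT-G and subscales score of Intervention Group and Control Group between baseline (T0") and T1, and likewise T2. No covariate is named.
- A longitudinal model: "A generalized estimating equation (GEE) model will be used to compare the difference in each outcome across different time points". Its terms, and whether the T0 score is a covariate or one of the repeated outcomes, are not given.

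The section opens by stating that "an intention-to-treat analysis will be used in line with the CONSORT statement". It also plans tests of patient characteristics "to test the homogeneity at baseline between groups".

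DASS-21 and FACT-G are collected at baseline, week 3 and week 6 (Procedure and Table 3). Each item under Hypothesis is a contrast with the control group. The Study sample section sizes the trial from one published trial in which "the effect sizes of anxiety and depression are 1.72 and 0.74, respectively". It takes the depression figure with a "type 1 error of 5% (α=0.05) and 90% power (β=0.05), two tails, the sample size is 80", raised to 84 for attrition.

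**The concern.** Every patient has a baseline score on the same instrument as the outcome. In a randomised trial, regressing the follow-up score on baseline gives a more precise arm difference than subtracting baseline, at any baseline-to-follow-up correlation below 1. The protocol fixes the less precise form, and the GEE sentence does not clearly supply the better one.

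Two further consequences follow.

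- The choice between t-test and Mann-Whitney depends on the data. The rank test does not estimate a mean difference, so the quantity being tested could differ between outcomes or visits. This could well arise: DASS-21 subscales are bounded at 0 to 21, there is no minimum distress score for entry, and patients under treatment for anxiety or depression are excluded.
- Each outcome and visit contrast will have a two-group test and a GEE result. If they disagree, the protocol has no rule for which one decides.

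At stake are precision that would cost nothing to gain and a clear answer for each hypothesis.

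**Working it through.** **Inputs.** From Study sample: d = 0.74, two-sided 5%, 90% power, 80 analysed (40 per arm). Assumed, because the protocol gives neither: the baseline-to-follow-up correlation rho, and the SD to which d refers. Also assumed: equal SDs at baseline and follow-up.

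**1. The plan's own figure.** For a two-sample t-test with 40 per arm, the noncentrality is 0.74 × √(40/2) = 3.31 on 78 df. Power is 90.5%; with 39 per arm it is 89.7%. So 80 is reproduced. Attrition: 80 × 1.05 = 84.

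Two separate slips do not affect this point. The text prints "90% power (β=0.05), two tails", but β = 0.05 would mean 95% power and 98 patients. The literature review gives a "medium effect size on depression (Cohen’s d= 0.72", against 0.74 in Study sample; 0.72 would need 84 before attrition.

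**2. Relative precision.** With the SD set to 1 at each visit:

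- variance of change = 2(1 − rho)
- variance after baseline adjustment = 1 − rho²
- ratio = 2(1 − rho) / [(1 − rho)(1 + rho)] = 2/(1 + rho)

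This gives 2/1.3 = 1.54, 2/1.5 = 1.33 and 2/1.7 = 1.18 at rho 0.3, 0.5 and 0.7. The ratio does not depend on the scale of d.

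**3. Power if d = 0.74 is on the raw-score SD.** The effect becomes 0.74/√(2(1 − rho)) for change and 0.74/√(1 − rho²) adjusted. Power is from the noncentral t at 40 per arm (78 df for change, 77 df adjusted).

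| rho | Change: effect | Change: power | Adjusted: effect | Adjusted: power | N for 90% power, change / adjusted |
|---|---|---|---|---|---|
| 0.2 | 0.585 | 73.4% | 0.755 | 91.5% | 126 / 76 |
| 0.3 | 0.625 | 78.9% | 0.776 | 92.9% | 110 / 72 |
| 0.4 | 0.676 | 84.7% | 0.807 | 94.6% | 96 / 68 |
| 0.5 | 0.740 | 90.5% | 0.854 | 96.5% | 80 / 60 |
| 0.6 | 0.827 | 95.5% | 0.925 | 98.3% | 64 / 52 |
| 0.7 | 0.955 | 98.8% | 1.036 | 99.6% | 50 / 42 |

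The change-score test drops below 90% only when rho is under about 0.49.

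**4. Power if d = 0.74 is already on the change-score SD.** The planned t-test has 90.5% whatever rho is.

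**5. Does the GEE recover the precision?** If T0 enters as a repeated outcome with a full arm-by-time structure and data are complete, the interaction contrast is the difference in mean change, the same estimate as the t-test. It gains only if T0 is a covariate or the baseline means are constrained equal across arms. The protocol states neither.

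**6. The rank-test switch.** Under normality the Mann-Whitney test has relative efficiency 0.955. That is equivalent to 40 × 0.955 = 38.2 per arm and gives 89.1% at an effect of 0.74, a loss of 90.5 − 89.1 = 1.4 points. The power cost is small; the issue is the change in what is tested.

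**The case against.** Several stronger readings are tempting, and the protocol does not support them.

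- *The trial is underpowered.* This needs d on the raw-score SD and rho below about 0.49. Neither is in the protocol, and 80 is right for its stated inputs.
- *Baseline is wasted.* A change score does use baseline. Since its variance is 2(1 − rho), it beats a follow-up-only comparison once rho exceeds 0.5.
- *The change score is biased by chance imbalance.* Over randomisation it is unbiased. Sensitivity to imbalance in a given sample is the precision point seen from another side.
- *The GEE does not compare arms.* Its sentence is loosely worded, but every hypothesis is a contrast with control in a two-arm trial, so a between-arm comparison over time is the natural reading.
- *Intention-to-treat is breached.* A change test omits patients without the later visit, but the GEE can use the visits that are available. Planned attrition is 5%, about 4 of 84, and missing-data handling is commonly left to a SAP.
- *Baseline tests distort the result.* Nothing makes the analysis depend on them.

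It is also fair to say that model terms often belong in a SAP. What stands is that the protocol does not leave the two-group test open: it fixes an unadjusted change score with a data-dependent switch, places a GEE beside it and ranks neither.

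**Conclusion.** The point holds as one of efficiency and clarity. The loss of precision relative to baseline adjustment is certain for any rho below 1: the variance is 18% to 54% larger over rho 0.7 to 0.3. Its effect on power is conditional. It ranges from none, if d is on the change-score SD or rho is about 0.5 or more, to 73% at rho 0.2 if d is on the raw-score SD. Over the same raw-score range the adjusted analysis stays at 91.5% or above. A shortfall against 90% is thus a possibility and not a finding; knowing the scale of d and the value of rho would settle it. The normality switch costs little power but makes the tested quantity depend on the data. The missing order between the two-group test and the GEE should be resolved before outcome data are seen.

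**What to change.** In Data analysis, name one deciding analysis for each outcome: the GEE already planned, or a mixed model, of the T1 and T2 scores with arm, visit, arm-by-visit and the T0 score of that outcome as covariate. Include all randomised patients with any post-baseline score, and report the arm difference with its 95% CI at each visit. Patients with no follow-up score still fall outside this model, so their number should be reported by arm. Keep the t-test and the Mann-Whitney test as sensitivity analyses only, so that no normality check decides which result counts.

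Whether one visit is to be primary, and whether to add a hospital term, are separate decisions for the sponsor; this point does not settle them.

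The cost is wording only. No patients, visits or data are added, and SPSS, the software named in the protocol, can fit the model.
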